### Statistical analysis

SPSS 25.0 software will be used for statistical analysis by data analysts who are blind to the study. Two-sided *P*-values will be calculated with a significant level of 5%, and the parameters will be estimated by 95% confidence intervals. The primary analysis will be under intention-to-treat (ITT) principle and be performed on both the ITT population and per-protocol (PP) population.

Descriptive statistics of demographic data and other baseline eigenvalues will be performed on the ITT population for both groups. Continuous variables will be presented as mean (SD) or median (IQR). Categorical variables will be presented as numbers (%). For continuous variables and categorical variables, *t*-test/rank sum test and chi-square test/Fisher exact test will be used to detect possible disequilibrium between groups.

The outcomes will be performed on both ITT and PP population. Initially, the number and percentage of HS cases and patients with mild-to-severe CMBs at baseline and annul follow-up will be calculated and compared between the two arms by Chi-square test or Fisher's exact test. Then, for all time-to-event models, cumulative event rate during the follow-up will be estimated using the Kaplan-Meier method and will be compared with the log-rank test. If needed, Cox proportional hazard regression analysis will be used after testing proportional hazard assumption and important potential covariates will be adjusted for sensitivity analyses. The mean and variability of serum lipid levels in 36 month follow-up with at least three measurements will be calculated and compared by Student *t*-test or Wilcoxon rank sum test. Then generalized linear mixed model will be used to analyze the correlation between the proportion of CMBs with different degrees and serum lipid levels over time.

The interim analysis will be performed when 172 subjects have completed at least one follow-up SWI, and it will be focused on subject recruitment, comparability of baseline between groups, sample size assumptions to account for event incidence, follow-up shedding rate, adverse event data, and the effect of treatment on the primary and secondary outcomes.

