**Outcomes:**

CHRISTMAS trial has co-primary outcomes, namely, hemorrhage risk: the incidence of HS and the changes in degree of CMBs until the end of 36-month follow-up.

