### Outcomes

#### Primary outcomes

The trial has co-primary outcome, namely, hemorrhage risk.

The first part is the incidence of HS confirmed by brain computed tomography (CT) or magnetic resonance imaging (MRI).

The second part is the changes in degree of CMBs until the end of 36 month follow-up.

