### Sample size estimates

Sample size calculations were based on the primary outcomes (the incidence of ICH). All participants are expected to be enrolled for 1 year and followed for 36 months. It will be tested whether the high-dose statin arm suffers a higher risk of hemorrhage than the low-dose statin arm in terms of the primary outcomes for 36 months. According to the SPARCL trial (the incidence of ICH: 25.2 vs. 12.0% in high-dose statin arm vs. low-dose statin arm with 4.9 years of mean follow-up duration) (17). The sample size was calculated by PASS software (version 15.0) with a two-sided type I error of 5% (α = 0.05) and 80% power, a sample size of 137 patients in each arm is required (total 274 patients). Assuming around 20% loss to follow-up, a total of 344 patients will be randomized.

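### Two primary outcomes are compared separately at an undivided 5% with no success rule, so the stated 5% error and 80% power need not apply to the hemorrhage claim

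*Protocol article*

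**What the plan says.** The Outcomes paragraph of the protocol article's abstract states: "CHRISTMAS trial has co-primary outcomes, namely, hemorrhage risk: the incidence of HS and the changes in degree of CMBs until the end of 36-month follow-up". The Primary outcomes section of the Methods puts this in the singular, "The trial has co-primary outcome, namely, hemorrhage risk", and then lists two parts. The first is HS confirmed on imaging. The second reads "The second part is the changes in degree of CMBs until the end of 36 month follow-up".

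The Statistical analysis section sets one level for everything: two-sided P-values "will be calculated with a significant level of 5%, and the parameters will be estimated by 95% confidence intervals". It then compares HS cases and CMB severity between the arms as separate quantities. It places the primary analysis under the ITT principle and adds that it will "be performed on both the ITT population and per-protocol (PP) population".

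The Sample size estimates section uses one of the two outcomes. It begins "Sample size calculations were based on the primary outcomes (the incidence of ICH", and the result is given "with a two-sided type I error of 5% (α = 0.05) and 80% power, a sample size of 137 patients in each arm is required". The same section says that the hypothesis of higher hemorrhage risk will be tested on the primary outcomes, in the plural. The article gives no effect size or power for CMB change. It also defines no composite, order of testing or division of alpha.

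**The concern.** The trial's hypothesis is that high-dose statin raises the risk of intracranial hemorrhage, and two separately tested outcomes bear on it. The article does not say whether one significant result supports the claim or whether both are needed. Each answer leaves one published design figure in doubt. If one is enough, the 5% is not the error rate of the claim. If both are needed, the 80% is not its power.

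This goes beyond detail that an article leaves to a fuller document. The article itself commits to an undivided 5% and to a power figure computed for one outcome, and the success rule bears directly on sample size. If HS and CMB change disagree, the article does not say what the trial has shown, and a rule chosen then would be chosen with the data in view. The planned interim analysis, which includes treatment effects on the primary outcomes, brings that moment forward.

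**Working it through.** **Inputs.** From Sample size estimates: ICH rates 25.2% and 12.0%, two-sided alpha 0.05, power 80%, 137 per arm, 20% loss, 344 randomized. From Statistical analysis: two-sided 5%, undivided. Not in the document, so assumed over a range: the correlation between the two test statistics (0 to 0.9) and the power for CMB change (80% to 95%).

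**1. The plan's own figure.** For two proportions with pooled variance under the null and no continuity correction, n per arm = [z(0.975)·√(2·p̄·q̄) + z(0.80)·√(p1q1 + p2q2)]² / (p1 − p2)².
- p̄ = (0.252 + 0.120)/2 = 0.186, so √(2 × 0.186 × 0.814) = 0.5503.
- √(0.252 × 0.748 + 0.120 × 0.880) = 0.5423.
- n = [(1.960 × 0.5503 + 0.8416 × 0.5423)/0.132]² = 135.2, so 136 against the stated 137.
- With 20% loss: 137/0.8 = 171.25, so 172 per arm and 344 in total.
- Power at 137 per arm: Φ[(0.132 × √137 − 1.960 × 0.5503)/0.5423] = Φ(0.860) = 80.5%.

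The arithmetic for the single outcome is therefore sound.

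**2. Either outcome suffices, each at two-sided 5%.** For independent tests the family-wise error is 1 − 0.95² = 9.75%. With correlation it is 1 − P(|Z1| < 1.96 and |Z2| < 1.96) under a bivariate normal. Counting false findings of harm only, it is 1 − 0.975² = 4.9% if independent, against 2.5% for a single test.

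**3. Both outcomes required at 0.05.** The error stays at or below 5%. Joint power is Φ2(z(HS power), z(CMB power); correlation), with HS power set to the stated 80%. It cannot exceed 80%, whatever the CMB power.

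| Correlation | Either suffices: two-sided error | Either suffices: false harm only | Both required: CMB power 80% | CMB power 90% | CMB power 95% |
|---|---|---|---|---|---|
| 0 | 9.75% | 4.9% | 64.0% | 72.0% | 76.0% |
| 0.3 | 9.5% | 4.8% | 66.6% | 73.7% | 77.0% |
| 0.5 | 9.1% | 4.5% | 68.7% | 75.1% | 77.9% |
| 0.7 | 8.3% | 4.2% | 71.3% | 76.9% | 78.9% |
| 0.9 | 7.0% | 3.5% | 75.0% | 79.1% | 79.9% |

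**4. HS first at 0.05, then CMB change at 0.05 only if HS is significant.** The error stays at 5%, and HS power stays at 80.5% with 137 per arm.

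**5. Holm.** At worst HS is tested at 0.025: Φ[(0.132 × √137 − 2.241 × 0.5503)/0.5423] = Φ(0.575) = 71.7%. When CMB change is significant at 0.025, HS is tested at 0.05. HS power therefore lies between 71.7% and 80.5%.

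**The case against.** The best defence is that how co-primary outcomes combine is commonly settled in a fuller protocol or SAP, and that the 5% sentence is a general convention, not a statement that each outcome alone supports a claim. An undivided alpha is correct if both parts are required or if HS is tested first. That stands in part: the undivided alpha is not an error in itself. But the article fixes the alpha and a one-outcome power without saying which of these rules applies, and the figures mean different things under each.

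The singular wording in Primary outcomes could suggest a composite. None is defined, however, and the Statistical analysis section compares the two parts separately. Nor do the sizing rates cover CMBs: they come from an earlier trial's ICH incidence, and the Introduction says that earlier studies had not looked at the question from the perspective of CMBs.

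Four stronger readings are tempting, and the document does not support them.
- A reader might infer that the trial must have either about 9–10% error or less than 80% power. Testing HS first avoids both.
- A reader might take 9–10% as the chance of a false finding of harm. It counts both directions. The harm direction alone is about 4.9% at most, and the two-sided figure falls to about 7% at high correlation.
- A reader might infer that a positive result in either the ITT or the PP population counts as primary. The sentence is awkward, but it names ITT as the governing principle.
- A reader might quote 64% as the trial's power, or lower figures from rescaling the 4.9-year rates to 36 months. The first assumes a CMB power and independence that the article does not give. The second is a separate question and needs an assumption about how the hazard behaves over time.

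**Conclusion.** The point holds as a missing decision rule that leaves one of two published figures unsupported. If either outcome suffices, two-sided family-wise error is about 7% to 9.75% for correlations from 0.9 down to 0, not 5%, and false harm is about half of that. If both are required, error is controlled and 80% is a ceiling on the power of the joint claim. The shortfall cannot be fixed because CMB power is unstated. It would be 5 to 16 percentage points if CMB power were also 80%, and negligible if CMB power were near 100%. The error figures rest on bivariate normal test statistics, and the power figures also take the article's event rates as given. Repeat comparisons at annual visits, the PP analysis and the interim look are further sources of multiplicity and are not counted here.

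**What to change.** State one rule before any unblinded look at outcomes, including the interim analysis. Make ITT the decision population and PP a sensitivity analysis. Any of these would do, with power restated to match:
- **Holm across HS and CMB change:** the smaller P-value against 0.025, then the other against 0.05. State HS power as at least about 72% at 137 per arm and the article's rates.
- **Both required at 0.05:** present 80% as the HS power only, not as the power for the joint claim.
- **Fixed sequence with HS first at 0.05:** HS power stays at about 80%, and CMB change is tested confirmatorily only after a significant HS result.

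This takes a sentence in the analysis section and a revised power statement, with no change to trial conduct. The downside is a somewhat less favourable stated power under the first two rules. Under the third, a CMB finding cannot support the claim by itself.

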## Introduction

Cerebral microbleeds (CMBs) are a crucial radiological marker of cerebral small vessel disease (CSVD) (1) to illustrate the micropathology of perivascular hemosiderin deposition corresponding to past small foci of bleeding (2). The prevalence of CMBs increases with age and exceeds 20% in community population over 60 years old (3, 4). More importantly, CMBs are also a common comorbidity of stroke, brain trauma, Alzheimer's disease, and cerebral amyloid angiopathy (5, 6), and are associated with cognitive impairment, psychiatric symptoms, and decline of daily living ability (7).

CMBs have been identified to be indicative of bleeding-prone microangiopathy for their dynamical accumulation over time, with the burden (presence and number) of baseline CMBs predicting the development of new CMBs in both deep and lobar regions, and may predict spontaneous intracranial hemorrhage (ICH) (8–12). These pieces of evidence have suggested an important link between the presence of CMBs and future macrobleeding. However, CMBs have also been demonstrated in approximately one-third of patients with ischemic stroke (IS), that are associated with an increased risk of recurrent IS, symptomatic ICH and death (13). As the burden of CMBs in IS patients increased, the relative and absolute risk ratios for ICH increase steeply, although the absolute incidence of recurrent IS is consistently higher than that of ICH (13–16). Therefore, it raises clinical dilemmas, particularly regarding the safety of secondary prevention treatment of IS with concomitant presence of CMBs.

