**Inclusion criteria**
1. Patients with a non-cardioembolic ischemic stroke within 14 days prior to entry to the study.
2. Adults between the ages of 18 and 90.
3. Patients with CMBs on baseline SWI imaging.
4. Patients or their legal representatives volunteer to participate and sign written informed consent.

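### The CMB co-primary is a change in degree, but the only between-arm CMB test stated compares categories visit by visit without using each patient's baseline

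*Protocol article*

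**What the plan says.** **Outcome.** Under Primary outcomes, the article states: "The second part is the changes in degree of CMBs until the end of 36 month follow-up".

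**Population.** Table 1 requires "Patients with CMBs on baseline SWI imaging". The Participants section adds that neither number nor location matters, so every patient starts with CMBs and the starting burden can vary widely.

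**Test.** Under Statistical analysis, the first step for CMBs is a tabulation of "patients with mild-to-severe CMBs at baseline and annul follow-up will be calculated and compared between the two arms by Chi-square test" or Fisher's exact test. No per-patient change or worsening variable is formed, and baseline degree does not enter the test.

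**Other models.** Kaplan-Meier and log-rank methods are planned for time-to-event models, but no CMB event is defined. Covariate adjustment is mentioned only with the Cox model, if needed, for sensitivity. The one longitudinal CMB model is described this way: a "generalized linear mixed model will be used to analyze the correlation between the proportion of CMBs with different degrees and serum lipid levels" over time. Randomised arm is not named in it.

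**Prognosis.** The Introduction describes CMBs as accumulating, "with the burden (presence and number) of baseline CMBs predicting the development of new CMBs in both deep and lobar regions".

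**The concern.** A change in degree belongs to a patient: it needs a start and an end. A chi-square test on categories at a visit sees only the end. Two patients who finish in the same grade count the same, even if one has worsened and the other has not. The test also treats ordered grades as unordered labels. The article itself names baseline burden as a predictor of new CMBs, and the stated test leaves that predictor out.

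The trial's hypothesis is one of harm. If the test of this co-primary is inefficient, a non-significant result could be read as reassurance about high-dose atorvastatin when the comparison had little chance of showing a difference. The sample size gives no protection, because it was set on intracranial haemorrhage alone.

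**Working it through.** **1. The plan's own figure.** The inputs are "two-sided type I error of 5% (α = 0.05) and 80% power" and "the incidence of ICH: 25.2 vs. 12.0% in high-dose statin arm vs. low-dose statin arm with 4.9 years of mean follow-up duration". With pooled variance and mean proportion 0.186:

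n = [1.96·√(2·0.186·0.814) + 0.8416·√(0.252·0.748 + 0.12·0.88)]² / (0.252 − 0.12)² = (1.0786 + 0.4564)² / 0.017424 ≈ 135.2, so 136 per arm.

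The article says "a sample size of 137 patients in each arm is required (total 274 patients", which agrees within one patient. Allowing for 20% loss, 137 / 0.8 = 171.25, so 172 per arm and 344 in total, as stated. The figure reproduces, but no rate, spread or effect for CMBs enters it.

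**2. Three-grade illustration (all CMB inputs are assumptions).** There are 137 patients per arm and 1,000 simulated trials per row. Baseline counts are log-normal, rounded, with a minimum of 1. New CMBs follow an overdispersed Poisson distribution with mean r·√(baseline count). Grades are 1–4, 5–10 and >10. Entries are power at two-sided 5%.

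| Log-mean, log-SD of baseline | r, low vs high dose | Chi-square on follow-up grade | Chi-square on grade worsening | Rank test, change in count | Baseline-adjusted log count |
|---|---|---|---|---|---|
| 0.7, 0.9 | 0.2 vs 0.45 | 0.11 | 0.46 | 0.88 | 0.89 |
| 0.7, 0.9 | 0.3 vs 0.6 | 0.14 | 0.46 | 0.87 | 0.88 |
| 0.7, 0.9 | 0.5 vs 1.0 | 0.28 | 0.70 | 0.93 | 0.96 |
| 1.0, 1.1 | 0.2 vs 0.45 | 0.09 | 0.46 | 0.90 | 0.92 |
| 1.0, 1.1 | 0.3 vs 0.6 | 0.11 | 0.50 | 0.87 | 0.89 |
| 1.0, 1.1 | 0.5 vs 1.0 | 0.20 | 0.63 | 0.92 | 0.95 |

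The rate ratio is 2 to 2.25. The correlation between baseline and follow-up log counts is 0.86–0.96, which is why a test that ignores baseline does poorly here.

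Two further simulations at 137 per arm and a doubled rate, with other assumed inputs, point the same way:
- In one, the follow-up-grade chi-square had 10–23% power, against 97–99% for a baseline-adjusted negative-binomial model of new CMBs.
- In the other, it had 11–39%, against 46–85% for baseline-adjusted grade or grade worsening and 91–98% for counts of new CMBs.

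Type I error was near 5% per test for the methods compared.

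**3. Two-category illustration.** Suppose a share b of patients is already above a single cut at baseline, and a further share of all patients crosses it during follow-up. The follow-up test compares b + 0.12 with b + 0.252; the change test compares 0.12 with 0.252. These rates are borrowed from the haemorrhage assumption only as an example.

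Power = Φ{[d·√137 − 1.96·√(2p̄q̄)] / √(p₁q₁ + p₂q₂)}

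Here d = |p₁ − p₂|, q = 1 − p, and p̄ is the mean of p₁ and p₂. For b = 0.40: (1.5450 − 1.3653) / 0.6903 = 0.260, so power is 0.603.

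| b | Follow-up test, 12.0% vs 25.2% crossing | Change test | Follow-up test, 25% vs 40% crossing | Change test |
|---|---|---|---|---|
| 0.30 | 0.590 | 0.805 | 0.730 | 0.758 |
| 0.40 | 0.603 | 0.805 | 0.797 | 0.758 |
| 0.50 | 0.655 | 0.805 | 0.909 | 0.758 |
| 0.60 | 0.762 | 0.805 | not meaningful (100% above the cut in one arm) | – |

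In the first setting the loss runs from about 4 points (0.805 − 0.762) to about 21 (0.805 − 0.590). In the second it runs from about 3 points to none, and the follow-up test sometimes does better.

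**The case against.** **The test is valid.** The arms are randomised, so a difference in follow-up grades is evidence of a treatment effect. Chance imbalance at baseline is already covered by the 5% error rate. This stands. A reader might infer that the plan has no randomised CMB comparison, or a biased one; the article does not support either.

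**The power loss is assumed, not documented.** This also stands. A reader might infer that most of the power is wasted, but the article gives nothing from which that could be shown, and the two-category table shows settings with little or no loss. Part of the largest contrast comes from replacing grades with counts rather than from using baseline: with grades kept, testing worsening raised power to 0.46–0.70, not to 0.9.

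**A 100% reading.** A reader might infer that the tabulated percentage is any CMB versus none, hence 100% in both arms at entry. The wording about differing degrees makes severity grades the more natural reading, so the point should not rest on this.

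**Other analyses and unseen documents.** The chi-square is introduced as a first step, and the time-to-event sentence is not confined to haemorrhagic stroke. But no CMB event is defined there, and the mixed model has lipid levels, which are measured after randomisation, where arm would be needed. The full protocol or analysis plan may say more, and details such as the covariate list may be left to it. The article nevertheless states both the outcome and its test, and those two do not match.

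**Conclusion.** The point holds as a mismatch between a defined co-primary outcome and its stated test, with a likely loss of efficiency. It is not a finding of bias or of an inflated error rate.

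Across the assumed three-grade scenarios with about a doubled rate of new CMBs and 137 per arm, power is:
- about 10–40% for the stated test;
- about 45–85% for baseline-adjusted grade or grade worsening;
- about 87–99% for analyses of change in count or baseline-adjusted count.

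These figures depend on several grades, a strong link between baseline and follow-up burden, and the assumed counts, cut-points and rates. None of these inputs is in the article. With a single cut the loss ranged from about 21 points to nil. The size is therefore uncertain; the mismatch itself does not depend on these assumptions.

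**What to change.** Keep degree as the endpoint. State how change in degree is obtained for each patient, and make the confirmatory CMB analysis one intention-to-treat comparison of arms at 36 months that uses baseline. An ordinal model of CMB grade with arm and baseline grade would do this. If all scheduled SWIs are used, an ordinal mixed model with an arm-by-time term, tested at 36 months, is the natural extension. Keep the visit-by-visit chi-square tables as description and label the lipid mixed model exploratory.

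If lesion counts are read from the same scans, add newly appearing CMBs per patient as a supporting analysis with a baseline-adjusted count model. Count them as new lesions rather than as follow-up total minus baseline total: the difference can be negative, which a negative-binomial model cannot take.

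The main change costs wording only, since the SWIs are already scheduled. The supporting analysis adds the work of counting. The change should be made before the interim analysis, which is to look at treatment effects on the primary outcomes.

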### Participants

By December 2023, 344 patients will have been enrolled. The inclusion and exclusion criteria are provided in Table 1. Briefly, patients are eligible if they (1) have a non-cardioembolic ischemic stroke within 14 days from the onset of the symptoms prior to the study participation; (2) are between the ages of 18 and 90; and (3) have the presence of CMBs (without differentiating the number or localization) on baseline susceptibility-weighted imaging (SWI) (Supplementary material 2). Key exclusion criteria include active hemorrhagic diseases, hemorrhagic tendency, severe stroke, or other severe conditions that are not eligible for clinical trials. In addition, patients who have contraindications to statins or need for intravenous thrombolysis, interventional therapy, anticoagulation, or dual antiplatelet therapy shall be excluded.

**Table 1 T1:** Inclusion and exclusion criteria.

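### The CMB co-primary outcome is a change in degree to month 36, but the one between-arm CMB test named compares status at each visit, which is valid but does not match the outcome and is inefficient

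*Protocol article*

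**What the plan says.** The Primary outcomes section, in line with the abstract, defines the CMB co-primary as a change: "The second part is the changes in degree of CMBs until the end of 36 month follow-up".

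The Statistical analysis section names one comparison of CMBs between the arms. The number and percentage of "patients with mild-to-severe CMBs at baseline and annul follow-up will be calculated and compared between the two arms", with a chi-square or Fisher's exact test.

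Two other analyses in that section could bear on CMBs:

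- The longitudinal model: a "generalized linear mixed model will be used to analyze the correlation between the proportion of CMBs with different degrees and serum lipid levels over time". It relates degree to lipids and does not name the randomised arm.
- The survival methods: "for all time-to-event models, cumulative event rate during the follow-up will be estimated using the Kaplan-Meier method", with a log-rank comparison and Cox regression if needed. No CMB-progression event is named.

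On who enters, Table 1 requires "Patients with CMBs on baseline SWI imaging", and the Participants section accepts patients who "have the presence of CMBs (without differentiating the number or localization) on baseline susceptibility-weighted imaging (SWI"). The Follow-up section schedules SWI at 1 month and annually after the baseline scan, so paired scans will exist for each patient still in follow-up.

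**The concern.** A change outcome asks whether patients moved from where they started. A percentage at a visit asks where they are. In this trial the two differ materially, because every patient has CMBs at entry and any number is eligible. A patient's degree at month 36 therefore depends on the degree at entry as well as on anything that happened under treatment. The Introduction itself describes "the burden (presence and number) of baseline CMBs predicting the development of new CMBs", so baseline burden is also prognostic for the outcome. A test that ignores it carries the entry spread as noise.

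The trial's hypothesis is one of harm. If the co-primary CMB test is weaker than it need be, a non-significant result could be read as reassurance about high-dose statin therapy when it is weak evidence. The article also reports no sample size or power for the CMB outcome, so nothing shows that there is power to spare.

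**Working it through.** **1. The plan's own figure.** Sample size estimates uses 25.2% versus 12.0%, two-sided α 0.05 and 80% power. With pooled variance under the null, mean proportion 0.186:

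n = [1.960·√(2·0.186·0.814) + 0.842·√(0.252·0.748 + 0.120·0.880)]² / 0.132² = (1.0785 + 0.4564)² / 0.017424 = 135.2, so 136 per arm against 137 stated. With 137 the power is 80.5%. Allowing for 20% loss, 137/0.8 = 171.25, so 172 per arm and 344 in total. The figure reproduces, but it is for ICH incidence. There is none for CMBs.

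**2. Assumptions for the comparison.** The article gives no CMB worsening rates and no baseline distribution of degree. I assume:

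- 137 evaluable patients per arm;
- three grades (mild, moderate, severe);
- a one-grade worsening probability of 25.2% versus 12.0% among patients who can still worsen (the ICH rates, used only as placeholders);
- no further worsening for patients already severe;
- six baseline mixes.

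**3. One mix by hand, 60/30/10.**

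- Share who worsen: 0.90 × 25.2% = 22.7% (high dose) and 0.90 × 12.0% = 10.8% (low dose). A 2×2 chi-square has 75% power.
- Month-36 status, high dose: mild 0.60 × 0.748 = 44.9%; moderate 0.30 × 0.748 + 0.60 × 0.252 = 37.6%; severe 0.10 + 0.30 × 0.252 = 17.6%.
- Month-36 status, low dose: 52.8%, 33.6% and 13.6% by the same steps.
- Noncentrality of the 2×3 chi-square = 137 × Σ(d²/2)/p̄, where d is the difference between arms and p̄ the mean share in each grade: 137 × (0.00642 + 0.00220 + 0.00503) = 1.87. On 2 degrees of freedom (critical value 5.99) the power is 21%.

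The same treatment effect therefore gives 75% power as change and 21% as status.

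**4. All six mixes, by the same formulas.**

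| Baseline mild/moderate/severe (%) | Power, month-36 status | Power, within-patient worsening |
|---|---|---|
| 34/33/33 | 12% | 60% |
| 50/30/20 | 16% | 69% |
| 60/30/10 | 21% | 75% |
| 70/20/10 | 26% | 75% |
| 80/15/5 | 36% | 78% |
| 90/8/2 | 50% | 80% |

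Simulation of this set-up gave 11–51% against 60–80%.

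**5. Other assumptions.**

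- If the rates are rescaled so that 25.2% and 12.0% of all patients worsen, status has 22–51% power and change about 80–82%.
- In a count-based model where high dose yields 1.8 times as many new CMBs, status has 10–28% and change 33–59%.
- In that same type of model with 80% of patients starting with one CMB, status has 22–58% and change 46–79%, and the ratio between them falls to 1.06–2.1.

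Under the null, both tests reject about 5% of the time.

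**The case against.** The strongest reply is that randomisation balances baseline degree in expectation, so a systematic difference in month-36 degree can arise only from different change. This stands. A reader might infer that the co-primary question is never tested or that the comparison is invalid. The documents do not support that: the status comparison is unbiased and holds its type I error, and the defect is mismatch and inefficiency.

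A second reply is that the outcome wording never says within-patient, and that tabulating degree by visit is a group-level way to describe change. That softens the contradiction. It does not supply a test of change, because each visit's percentages are compared between arms separately.

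A third is that this is a condensed article, and that a CMB-progression event could sit under the time-to-event methods. The text names no such event. The article does state both the outcome and its test, and the two differ, so this is more than omitted detail.

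Two stronger readings should be set aside. If the tested category meant any CMB, both arms would stand at 100% at baseline and the test would have almost no power. But the outcome speaks of degree, and the mixed model in the same section speaks of different degrees, so a graded reading is the natural one. It is also tempting to say that most of the power is lost whatever the circumstances. That fails when nearly all patients start mild, where the loss is less than half.

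**Conclusion.** The mismatch is real and sits in the current text: the outcome is change, while the only between-arm CMB test named is of status by visit. The month-36 comparison is a valid but inefficient test of a treatment effect on degree, and the baseline comparison carries no information on treatment.

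Under the main assumptions, power is about 11–51% for status against about 60–80% for within-patient worsening. More than half is lost in five of six baseline mixes; the smallest loss is about 50% against 80%, when 90% start mild. The direction was the same in every scenario examined, but the size rests on CMB rates and baseline mixes that the article does not give, and in some count-based scenarios the gain is small. The change test is no guarantee of adequate power either: in the less favourable count-based scenarios it reaches only 33–59%.

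**What to change.** In the Statistical analysis section, name as the co-primary CMB test a between-arm comparison of each patient's change in degree from the baseline SWI to the month-36 SWI, either worsened versus not or number of degrees gained. An ordinal model of month-36 degree by arm, adjusted for baseline degree, would also serve and avoids reducing the change to two categories. Keep the visit-by-visit numbers and percentages as description, without a test at baseline.

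The cost is one paragraph of wording and a little more analysis work. Baseline and annual SWI are already scheduled, so no new data and no added patients are needed. The wording is best settled before the interim analysis, because that analysis is to look at the effect of treatment on the primary outcomes.
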